### Health economic evaluation

An economic evaluation will be conducted from a societal perspective. At the conclusion of the 8-week treatment period, the costs associated with electroacupuncture or exercise therapy will be summarized. Since participants will not be permitted to undergo any other treatments during the study period, only study-related direct medical costs and direct non-medical costs will be calculated. These include registration fees, treatment fees, transportation costs, and any associated delays. Direct medical costs will encompass registration and treatment fees. The registration fee for each treatment will be estimated based on the patient’s self-reported choice of registered doctor. Treatment fees will be determined according to the real-time treatment prices provided by the National Medical Security Bureau. Non-medical costs will be derived from patient-reported values. QALYs for each patient over the study period will be computed using EQ-5D-5L and SF-6D from the multiple imputed dataset. Cost-effectiveness analysis will be conducted by calculating the ICER between the two groups. Missing data in the costs will be imputed by intra-group mean values.

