## Methods

### Study design

This will be a pragmatic, two-arm, randomized controlled trial conducted in 2 centers in China. A total of 196 KOA patients will be randomly assigned to the electroacupuncture group and the exercise group in a ratio of 1:1. The trial duration will be 24 weeks, comprising 8 weeks of treatment and 16 weeks of follow up. The study protocol has been approved by The Ethics Committee of Dongzhimen Hospital Affiliated to Beijing University of Chinese Medicine (2022DZMEC-165-02) and Peking University People’s Hospital (2021PHB431-001), and registered on Chinese Clinical Trial Registry (ChiCTR2300070376. Date: April 04, 2023. Version 1.0.). This protocol will be reported in accordance with Standard Protocol Items: Recommendations for Interventional Trials (SPIRIT) [22]. Fig 1 illustrates the SPIRIT schedule. S1 File shows the SIPRIT checklist and S2 File shows the original protocol approved by the ethics committee.

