### Interventions

For patients with unilateral knee osteoarthritis, treatments will be performed on the affected side which will be defined as the evaluating side. For those with bilateral osteoarthritis, treatments will be performed on both knees, with the more serious side being evaluated. In the event of similar conditions on both sides, flipping a coin to decide which side to evaluate. For both groups, the compliance of the intervention will be recorded. Any other treatment that may affect symptoms during the trial is prohibited, including drug therapy (NSAIDs, opioids, etc.) and physical therapy (tuina, hydrotherapy, etc.). When necessary, patients can receive Diclofenac Sodium Enteric-coated Tablets (Voltaren, Beijing Novartis Pharma Co., Ltd) as the rescue medication, except within 48 hours prior to the evaluation; timing and dosage will be documented meticulously. Education will be accompanied by both interventions, in a form of simulating doctor-patient communication in real treatment environment. This will include information regarding the definition, clinical manifestation, diagnosis, etiology, risk factors, anatomy of the knee joint, treatment, prevention measures and pain manage of KOA, with the aim of helping patients to better understand the condition. In addition, patients with a Body Mass Index (BMI) >25 will be encouraged to lose weight.

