Daily Physical Activity level (DPA): DPA contains 1 week’s daily average steps and walking time, which will be recorded by portable pedometers (Polygon H-215G; Bestek Electronics Co., Ltd, Taiwan, China). The patient will be provided with a pedometer at the commencement of the preparatory period. The pedometer is required to be worn at all times except sleeping, bathing and water sports. At each visit, the researcher will record the data collected by the pedometer for the preceding week.

Rescue medicine: Any use of rescue medicine will be recorded, including the time and dosage.

The Credibility/Expectancy Questionnaire will be measured within a 5-minute period following the initial treatment session. PGA will be measured at week 4, 8, 16 and 24. Rescue medicine will be recorded within 24 hours after each taking. Other secondary outcomes will be assessed at baseline and at week 4, 8, 16 and 24. Additionally, the NRS and the KOOS ADL will be assessed at week 4, 16 and 24 as secondary outcomes.

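### The cost side of the ICER omits the rescue drug that the protocol permits and records, and fills missing costs with arm means although the QALYs are multiply imputed

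*Protocol article*

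**What the plan says.** Comparing cost-effectiveness is the second of the two aims at the end of the Introduction. The Health economic evaluation section takes a societal perspective and sets these rules:

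- **Costs.** "At the conclusion of the 8-week treatment period, the costs associated with electroacupuncture or exercise therapy will be summarized". The items listed are registration fees, treatment fees, transport and delays. Direct medical costs are registration and treatment fees only; there is no drug item.
- **Reason for the short list.** "Since participants will not be permitted to undergo any other treatments during the study period", only study-related costs are counted.
- **QALYs.** "QALYs for each patient over the study period will be computed using EQ-5D-5L and SF-6D from the multiple imputed dataset".
- **Missing costs.** "Missing data in the costs will be imputed by intra-group mean values".

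Other sections bear on these rules:

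- **Study design:** "The trial duration will be 24 weeks, comprising 8 weeks of treatment and 16 weeks of follow up".
- **Secondary outcomes:** "Other secondary outcomes will be assessed at baseline and at week 4, 8, 16 and 24", which covers both utility instruments. The same section records any use of rescue medicine with its time and dosage.
- **Interventions:** other treatment that may affect symptoms is prohibited during the trial, but "When necessary, patients can receive Diclofenac Sodium Enteric-coated Tablets". Compliance with the intervention is recorded in both groups.

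**The concern.** Two stated rules do not fit the rest of the protocol.

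First, the cost list is short because, on its own reasoning, there is nothing else to cost. The Interventions section contradicts that: a drug is available on need throughout, and its use is logged. Rescue use responds to pain, and pain is one of the two primary outcomes on which the arms are being compared, so its cost may well differ between arms. The recording rule has no end date, so I read it as running to week 24, the same span as the QALYs.

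Second, the two halves of the ICER treat missing data differently. Utilities are multiply imputed; costs get a single constant per arm. A constant carries no information about the patient and no uncertainty, and it breaks the link between a patient's cost and QALY.

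At stake is the credibility of the answer to one of the trial's two aims. The primary outcomes are not affected.

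**Working it through.** The economic section states no figure that could be reproduced, and the article gives no costs or utilities, so no corrected ICER can be computed. What can be checked is the logic of the omission and the effect of arm-mean filling.

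**1. Omitted rescue cost**

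Let ΔC be the planned cost difference, ΔE the QALY difference, and r_EA and r_EX the mean rescue drug cost per patient in the electroacupuncture and exercise arms.

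- Planned ICER = ΔC/ΔE.
- ICER with rescue costed = (ΔC + r_EA − r_EX)/ΔE.
- Relative error = (r_EA − r_EX)/ΔC.

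If rescue cost is equal in the two arms, the error is zero. If it differs, the arm with more rescue use looks cheaper than it is. Neither r is in the document, so direction and size stay open.

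**2. Standard error after arm-mean filling**

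Inputs: N = 98 per arm (Abstract). The share of missing costs is an assumption. The 20% case borrows the dropout allowance in the Sample size section; no missing-cost rate is given, so a range is shown.

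With m of N costs observed and sample variance S²:

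- The filled values sit at the mean and add no squared deviation, so the variance of the filled data is S²(m−1)/(N−1).
- Naive SE² = S²(m−1)/[(N−1)N]; correct SE² = S²/m.
- Ratio of SEs = √{[(m−1)/(N−1)] × (m/N)}.

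At 20% missing, m = 78: √[(77/97) × (78/98)] = √(0.794 × 0.796) = 0.795. A nominal 95% interval then covers 2Φ(1.96 × 0.795) − 1 = 88.1%.

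| Missing | m | SE ratio | Coverage of nominal 95% |
|---|---|---|---|
| 5% | 93 | 0.949 | 93.7% |
| 10% | 88 | 0.897 | 92.1% |
| 20% | 78 | 0.795 | 88.1% |
| 30% | 69 | 0.703 | 83.1% |

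A simulation of 20,000 trials (skewed costs with mean 1,000, 78 of 98 observed per arm, missing completely at random) agrees: mean naive SE 63.4 against an empirical SE of 80.0, and coverage 87.7%. The mean error in the cost difference was 1.2 on that scale of 1,000, that is, about zero.

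**3. Cost-QALY link**

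Patients with filled costs have a cost deviation of zero, so they add nothing to the cross-product with QALYs. The within-arm covariance falls to (m−1)/(N−1) = 77/97 = 0.794 of its observed value at 20% missing. Any joint measure of uncertainty computed from the filled data inherits this.

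**4. Point estimate when missingness is informative**

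As an illustration, suppose the 20% with missing costs attended only a fraction f of sessions while everyone else attended all. In units of a full course, the true arm mean is 0.8 + 0.2f and the filled mean is 1.

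- f = 0.25: 1/0.85 − 1 = 17.6% too high.
- f = 0.50: 1/0.90 − 1 = 11.1% too high.
- f = 0.75: 1/0.95 − 1 = 5.3% too high.

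This carries into the cost difference unless it happens to cancel between arms.

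**The case against.** The strongest defence concerns the time windows. A reader might infer that totalling costs at week 8 and QALYs over 24 weeks is itself an error. The document does not support that. Both courses end within 8 weeks and other treatment is prohibited throughout, so the cost of the therapies themselves is complete at week 8 while benefit may continue. Setting that cost against 24-week QALYs is legitimate. The unequal windows matter only through costs that arise later: rescue drug, which the protocol itself foresees, and any adverse-event or off-protocol care. For the same reason, the 16 uncosted weeks out of 24 are a share of calendar time and not of cost. Cutting the QALYs back to 8 weeks would discard real benefit.

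Further objections carry weight:

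- Omitted costs bias the difference only if they differ between arms, and arm-mean filling leaves the mean unbiased if costs are missing completely at random. Both are correct, so bias is possible but not shown.
- A reader might infer that early stoppers will be given full-course costs. The text does not say so. An unattended session has no cost rather than a missing one, and pricing from attendance fits the stated tariff approach. Missingness may be confined mainly to patient-reported items.
- The article names no standard error or interval for the ICER. The shrinkage therefore applies to whatever is computed from the filled data. The absence of intervals or acceptability curves is not held against the plan, since the full protocol or SAP may contain them.

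None of this removes the contradiction over rescue medication or the stated single-value fill.

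**Conclusion.** The point holds in two parts, and both should be corrected.

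- **Rescue medication.** The ground given for the narrow cost list conflicts with the permitted and recorded rescue drug. A potentially differential cost is left out of a societal evaluation over the full 24 weeks. Size and direction cannot be derived from the document.
- **Missing costs.** The arm-mean rule is a weak choice beside multiply imputed utilities. On the assumption of 20% missing costs, it understates the standard error of mean cost by about 20%; over 5% to 30% missing, by about 5% to 30%. It also weakens the cost-QALY covariance. It biases the cost difference only if costs are not missing completely at random; the 5% to 18% overstatement of an arm's mean treatment cost rests on the assumed attendance pattern.

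The document does not support the stronger conclusions that the ICER is biased, or that an 8-week cost total set against 24-week QALYs is wrong in itself.

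**What to change.** In the Health economic evaluation section:

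1. Keep the 24-week QALY horizon. Add the recorded rescue medication to direct medical costs over the same 24 weeks.
2. Correct the premise that no other treatment is permitted so that it agrees with the Interventions section. This concerns costing only; no clinical rule needs to change.
3. Compute session fees from recorded attendance, so that a session not attended counts as zero cost and not as missing.
4. Replace the arm-mean fill. Impute the remaining missing costs jointly with the utilities by multiple imputation within arm, and carry any uncertainty calculation through the same imputed datasets.

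Rescue use and attendance are already recorded, and multiple imputation is already planned for the outcomes. The downside is a little more analysis work.

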Intervention for the management of KOA is varied. Exercise showed strong evidence in managing KOA, with multiple forms of exercise delivery proven to be better than non-exercise [8–11]. Acupuncture is another nonpharmacologic therapy which showed favorable evidence. Compared to the sham acupuncture, acupuncture can relieve pain and dysfunction [12–14]. Considering the safety and potential benefits, acupuncture was partly recommended by certain guidelines [6,7,15]. Electroacupuncture is the type of acupuncture recommended for research by National Institute for Health and Clinical Excellence. Its potential better effect was observed in our previous study [13]. Benefits to the convenience and standardization of operation, electroacupuncture is more widely used in clinical practice. In early studies focused on both acupuncture and exercise, acupuncture was designed to be a supplement [16–18]. Considering the cost of time and expenses, it can be difficult for patients to adopt multiple nonpharmacologic therapies. The popularity of acupuncture and exercise varies across different regions. Understanding their respective advantages and characteristics can provide a basis for personalized selection. For lack of attention, evidence regarding the differences between acupuncture and exercise is insufficient. To our knowledge, only one trial compared acupuncture with exercise directly [19]. However, the inclusion of patients in surgery waiting list was limited in generalization. From an economic point of view, both acupuncture and exercise were proved to be cost-effective options for KOA in the developed countries. In a German study compared acupuncture with routine care in treating KOA, the overall Incremental Cost-Effectiveness Ratio (ICER) was 17,845 Euros per Quality-Adjusted Life Year (QALY) gained [20]. In another Denmark study compared supervised exercise with education, the ICER ranged from 6,229 to 20,688 Euros per QALY [21]. However, few studies focused on the difference between the cost-effectiveness of acupuncture and exercise directly. Meanwhile, due to economic and medical resource constraints in developing countries, the cost-effectiveness of acupuncture and exercise may be disparate from that in developed countries. To save conserve resources, it is necessary to find the more cost-effective therapy.

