This randomized controlled trial aims to: (1) evaluate the effectiveness of electroacupuncture versus exercise in alleviating pain and improving function in patients with KOA; (2) compare the cost effectiveness of acupuncture and exercise in treating KOA.

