### Statistical analysis

SPSS 26.0 software will be used for statistical processing. Measurement data will be expressed as mean and standard deviation, or median and interquartile ranges. Counting data will be expressed as percentages.

All randomly grouped patients with at least 1 session of intervention received will be included in the modified intention-to-treat (mITT) analysis. Multiple imputation will be used to fill the missing data. Five datasets for the missing data will be imputed by the observation value of age, gender, body mass index, KL grade and outcomes from other timepoints. All between-group comparison on repeated measure continuous outcomes (NRS, KOOS ADL, KOOS QOL, SF-6D, EQ-5D-5L, 30s-CST and 40m FPWT, DPA, except PGA) will be assessed by mixed-effect models using outcome scores at all assessed timepoints as the dependent variable, intervention as the main factor, and the baseline value as the covariate. PGA will be assessed by chi-squared test. Sensitivity analysis will be conducted on the primary outcomes (NRS and KOOS ADL) in 2 datasets. First, the dataset without imputation will be analyzed to address potential imputation bias. Second, the per-protocol (PP) set, which will be defined as receiving a minimum of 19 (electroacupuncture) or 12 (exercise) sessions with no obvious protocol violation, will be analyzed to address the compliance. For primary outcomes, *P* < 0.025 will be considered statistically significant (Bonferroni correction). Secondary outcomes will be considered exploratory, and *P* < 0.05 will be considered statistically significant.

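### The second aim rests on a point ICER, with no stated baseline-utility adjustment of QALYs and no stated sampling uncertainty

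*Protocol article*

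**What the plan says.** The Introduction gives as the second of two aims to "compare the cost effectiveness of acupuncture and exercise in treating KOA", and motivates it with the statement that "it is necessary to find the more cost-effective therapy".

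The Health economic evaluation section then describes the method in some detail: perspective, cost items, price source, utility instruments and the handling of missing data. On QALYs it says: "QALYs for each patient over the study period will be computed using EQ-5D-5L and SF-6D from the multiple imputed dataset". On missing costs: "Missing data in the costs will be imputed by intra-group mean values". On the comparison itself: "Cost-effectiveness analysis will be conducted by calculating the ICER between the two groups". It mentions no covariate for baseline utility, no interval, no bootstrap and no threshold, and it does not say which of the two instruments leads.

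The Statistical analysis section lists EQ-5D-5L and SF-6D among the repeated continuous outcomes. It analyses them in mixed-effect models with "intervention as the main factor, and the baseline value as the covariate". QALYs are not in that list.

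**The concern.** A QALY over the study period contains the baseline utility directly, and also indirectly, because patients who start higher tend to stay higher. A chance difference between arms at baseline therefore passes into the QALY difference, which is the denominator of the ICER. The plan removes that noise when the two instruments serve as secondary outcomes, but does not say so when they serve one of the two aims.

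The ICER is also a ratio of two estimated differences. Quoted as a single value, it does not show whether cost and QALY differences of that size would arise by chance. The primary and secondary outcomes have stated significance levels; the economic comparison has no stated way to express uncertainty. At stake is whether a report that one therapy is cheaper and better reflects the therapies or the draw of patients.

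**Working it through.** **The plan's own figure.** The economic section states no number to reproduce. The sample size, used here only for the arm size, does reproduce: n = 2(z₀.₉₈₇₅ + z₀.₈₀)²/0.5² = 2(2.241 + 0.842)²/0.25 = 76.04, so 77 per arm. The t-test version needs 78, and 78/0.8 = 97.5, so 98 per arm and 196 in total. It is sized on the NRS and KOOS ADL, not on QALYs.

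**Inputs.** From the protocol: utilities at baseline and weeks 4, 8, 16 and 24; 24 weeks in total; 98 per arm. Assumed, because the protocol gives neither: a between-visit utility correlation ρ of 0.3 to 0.7, and a utility SD of 0.15 (range 0.10 to 0.20), equal at all visits. The trapezoid rule is also an assumption.

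**Step 1: weights.** In weeks, the trapezoid weights are 2, 4, 6, 8 and 4, which sum to 24. Baseline carries 2/24 = 8.3% directly; the follow-up weights sum to 22.

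**Step 2: share of the variance due to baseline.** In units of the utility variance, the covariance of the QALY with baseline utility is 2 + 22ρ. The share explained is R² = (2 + 22ρ)²/V, where V is the variance of the weighted sum. Two correlation patterns give the range:

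- (a) all pairs of visits correlate ρ: V = 136(1 − ρ) + 576ρ
- (b) baseline with follow-up ρ, follow-up visits with each other 0.7: V = 4 + 88ρ + 378.4, where 378.4 = 0.3 × 132 + 0.7 × 484

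| ρ | (2 + 22ρ)² | V (a) | R² (a) | V (b) | R² (b) |
|---|---|---|---|---|---|
| 0.3 | 73.96 | 268.0 | 0.276 | 408.8 | 0.181 |
| 0.5 | 169.00 | 356.0 | 0.475 | 426.4 | 0.396 |
| 0.7 | 302.76 | 444.0 | 0.682 | 444.0 | 0.682 |

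These shares depend neither on the utility SD nor on the number of patients.

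**Step 3: absolute size**, for SD 0.15, ρ = 0.5, pattern (a), complete data.

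- SD of the QALY = 0.15 × √356/52 = 0.0544.
- Unadjusted SE = 0.0544 × √(2/98) = 0.0078; 95% half-width 0.015.
- Adjusted SE = 0.0078 × √(1 − 0.475) = 0.0056; 95% half-width 0.011.
- For utility SD 0.10 to 0.20 the half-widths are 0.010 to 0.020 unadjusted and 0.007 to 0.015 adjusted.
- A one-SE baseline imbalance is 0.15 × √(2/98) = 0.021. With slope 13/52 = 0.25 QALY per utility unit, it moves the QALY difference by about 0.005.
- With 77 complete patients per arm, both SEs rise by √(98/77) = 1.13.

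**Step 4: what a point ICER shows when nothing differs.** One arm appears dominant when the cost and QALY differences have opposite signs. If the two differences are independent and centred at zero, the probability is ½ × ½ + ½ × ½ = ½; a simulation of 200,000 trials gave 25.0% each way. If they correlate r, it is arccos(r)/π, which is 40% at r = 0.3 and 60% at r = −0.3. The remaining trials give a positive ratio of arbitrary size. If QALYs are equal but one arm is clearly dearer (simulated at five SEs of the cost difference), the dearer arm appears dominated in about 50% of trials and appears to buy QALYs in the rest.

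**The case against.** The strongest objection is that this reads a method from silence. The article condenses a fuller protocol, filed as a supplement and not shown, and an analysis plan may exist. Bootstrap intervals, acceptability curves, thresholds and the choice of base-case instrument are often left to such documents. The article nowhere says that QALYs will be unadjusted or that uncertainty will go unreported. This stands, and it limits the point: it concerns what the article selects as its analysis, not a demonstrated error. What remains is that the section is specific on nearly everything else, names one comparison, and does not carry over a covariate that the plan fixes for the same scores. Adjusting the scores and then computing QALYs is not a contradiction, but the difference in treatment has no stated reason.

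A reader might infer more than the documents support:

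- **That the rule ranks the therapies in every trial.** It does not. No threshold is stated, so a point ICER orders the therapies only under dominance, about half of null trials. Otherwise it reports a trade-off.
- **That the unadjusted QALY difference is biased.** Randomisation makes it unbiased on average. Adjustment removes chance imbalance and gains precision, and it does not touch the cost difference.
- **That most of the result is baseline imbalance.** In these calculations that is so at correlations of about 0.6 and above (53–58% at 0.6), and the correlation is assumed.
- **That session counts (24 against 16) drive the costs.** The protocol gives no unit prices, and fees, transport and delays also enter.

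Adjustment would not lower the one-in-two rate of apparent dominance under no difference either. Only an interval deals with that.

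**Conclusion.** The point holds in a limited form. For one of the trial's two aims, the article names only a point ICER from patient-level QALYs, without a stated baseline-utility adjustment or a statement of uncertainty. The avoidable part of the variance of the QALY difference is about 18–28% at correlation 0.3, 40–47% at 0.5 and 68% at 0.7. This rests on trapezoid QALYs at the five scheduled visits, equal SDs and complete data. The figure of about one half for chance dominance rests on no true difference in cost or QALYs and on independence of the two estimates.

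This is a worthwhile improvement to an otherwise specific section. It neither invalidates the economic evaluation nor affects the primary outcomes or the sample size.

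**What to change.** In the Health economic evaluation section, before anyone sees results by arm:

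1. Estimate the QALY difference by regressing each patient's QALY on arm and on the baseline utility from the same instrument, and use that adjusted difference in the ICER.
2. Report joint cost-QALY uncertainty from a bootstrap that resamples patients within arm, keeps each patient's cost and QALY together, and is combined across the imputed datasets. Net benefit over a stated range of thresholds is one suitable presentation.
3. Bring missing costs into the multiple imputation. Filling them with the arm mean shrinks the cost variance, so an interval built on those costs would be too narrow.
4. State which utility instrument is the base case; the other becomes a sensitivity analysis.

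If the unshown protocol or analysis plan already contains these steps, a sentence pointing to it is enough. The cost is a few sentences and some code; EQ-5D-5L and SF-6D are already collected at baseline, so no patients, visits or data are added. The real downside is that the trial may have to report that neither therapy is clearly more cost-effective.
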